**Group therapy**

Designated personnel at the trial center will input basic information of eligible patients into the randomization system according to the randomization table. A random number will then be generated. Patients who meet the inclusion criteria will undergo random allocation after obtaining signed informed consent.

Both patient groups received conventional treatments, including chemotherapy, traditional Chinese medicine, and instrument therapy, with treatment selection and plans based on the guidelines for diagnosis and treatment of premature ejaculation. To maximize the effectiveness of CBT interventions based on mobile devices in PE patients, we used remote management through social media software (WeChat) to address sensitive issues that may be difficult to reach in the population. We used the WeChat-MiniApp: "PE-CBT" developed by Hangzhou Kang Ming Information Technology Co., Ltd. to remotely manage the intervention group of patients. WeChat management mainly includes: (1) patients can achieve out-of-hospital coordination and management through WeChat and learn courses on cognitive-behavioral therapy; (2) researchers can track patient management through outpatient clinics (Fig 1). The specific course schedule is shown in the Fig 2. The entire course is divided into three stages. The stage 1 focuses on improving cognition, the stage 2 focuses on improving behavior, and the stage 3 focuses on reviewing.

**Patient compliance and withdrawal**

To ensure patients' compliance with the study, the research team will adopt a grid-based approach, such as telephone and internet reminders, to prompt patients to attend follow-up appointments at the outpatient clinic before the scheduled time. Meanwhile, during each follow-up visit, the research team will emphasize that patients in the intervention group should complete the relevant WeChat learning according to the requirements.

**Availability of investigational drugs/treatments**

This study does not involve the exploration of pharmaceutical/medical device interventions.

**Administration method and dose adjustment**

This study does not involve the exploration of pharmaceutical/medical device interventions.

**Adverse Event Reporting**

Any adverse event, whether causally related to the intervention or not, that occurred from the time the subject signed the informed consent and was enrolled in the trial until the end of the trial. Any medical occurrence prior to the administration of the intervention on day one medical condition or clinically significant laboratory abnormality that occurred prior to the administration of the intervention on Day 1 is considered pre-existing and must be documented in the case report The case report form must be documented. All AEs occurring after the administration of the intervention until the last day of the study (including follow-up, pause in the study) must be documented on the case report form. All AEs occurring after the administration of the intervention until the last day of the study (including follow-up, study pause) must be documented accordingly.

When completing the adverse event form, the investigator will use a scale of "1 to 5" to describe the severity of the adverse event.

To standardize the criteria, the intensity of the adverse event will be determined by reference to the CTCAE v3.0 grading definitions: Grade 1 (mild, asymptomatic or with mild signs; clinical or diagnostic observations only; no intervention required), Grade 2 (moderate, requiring minimal, local or non-invasive treatment; age-appropriate instrumental limitation of activities of daily living), Grade 3 (severe or clinically significant but not immediately life-threatening; hospitalization or extended hospitalization; disabling; limited ability to perform activities of independent living), Grade 4 (life-threatening, requiring urgent treatment), and Grade 5 (death).

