**Eligibility criteria**

Patients meeting the following inclusion criteria were recruited: (1) male aged between 18-40 years; (2) in a stable heterosexual relationship with the same partner for at least 6 months; (3) diagnosed with PE according to the ISSM definition and not medically managed for at least 7 days; (4) able to use mobile devices such as smartphones and tablets; and (5) having read and agreed to sign the informed consent form.

Patients' exclusion criteria are as follows: (1) primary premature ejaculation patients; (2) patients taking medications such as amphetamines, dopamine, etc. that may cause PE; (3) patients with cognitive impairment, communication disorders, visual impairment, hearing impairment; (4) patients with other complex male genital diseases; (5) patients with malignant tumors; (6) patients participating in other clinical trials; (7) patients deemed unsuitable for this study by the researchers. This trial does not involve exploration of drug/medical device interventions.

Participants will be considered for withdrawal from the study under the following circumstances. However, even if participants do not withdraw their consent to participate in the study, they will no longer be considered as trial subjects and will not be included in the analysis of the study as soon as they withdraw from treatment under the following circumstances:

(1) If participants voluntarily withdraw (including dropping out, actively withdrawing, etc.);

(2) If the researcher requires the participant to withdraw due to disease deterioration or other reasons;

(3) If the researcher considers the participant no longer suitable to continue participating in the study.

The researchers will conduct preliminary eligibility screening and collect written informed consent from selected participants prior to baseline evaluation. If data collection is not included in the initial informed consent process of the main clinical trial, each participant in the ancillary study must sign a consent form.

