**Statistical methods**

All data will be entered by two members separately and analyzed after confirming that the data is completely consistent. We will use SPSS 22.0 for statistical analysis. For metric data, Shapiro-Wilk test will be used to check for normality. If it meets the normal distribution, it will be described by mean ± standard deviation; otherwise, it will be described by median (P25, P75). Pearson correlation analysis will be used to evaluate the correlation, and P<0.05 will be considered statistically significant. Metric data of different groups will be described statistically using mean, standard deviation, median, minimum value, and maximum value. Count data of different groups will be described statistically using frequency (composition ratio). We will use exact probability calculation or non-parametric test to analyze the changes before and after intervention in each group. Regarding drop-out analysis, we will describe the actual number of enrolled subjects, excluded subjects, and drop-out subjects one by one, and analyze the specific reasons for drop-out and exclusion. The balance analysis of baseline values will be compared using analysis of variance or exact probability calculation for demographic data and other baseline indicators to measure the balance of each group. We will list adverse events that occurred during the trial and describe the changes in laboratory test results before and after the trial, and the relationship with the intervention when abnormal changes occurred.

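### The withdrawal rule ends trial-subject status and analysis inclusion when treatment stops, while the AE rule runs to the last study day, so AEs of withdrawn participants may go unrecorded or unreported

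*Protocol*

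**What the plan says.** Three parts of the protocol bear on this.

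- **Eligibility criteria (withdrawal paragraph).** On stopping treatment under any of three circumstances, "they will no longer be considered as trial subjects and will not be included in the analysis of the study as soon as they" stop. The rule applies "even if participants do not withdraw their consent to participate in the study". The circumstances are voluntary withdrawal, a removal worded "If the researcher requires the participant to withdraw due to disease deterioration or other reasons", and the researcher's judgement that the participant is unsuitable to go on.
- **Adverse Event Reporting.** The AE period is defined by reference to the subject: "from the time the subject signed the informed consent and was enrolled in the trial until the end of the trial". The recording duty covers "All AEs occurring after the administration of the intervention until the last day of the study"; time in follow-up and any study pause count towards it, and entry in the case report form is mandatory. No exception is made for withdrawn participants.
- **Statistical methods.** "We will list adverse events that occurred during the trial". The same section also describes numbers and reasons for drop-out and exclusion.

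The Primary outcome measures section has follow-up at day 1, week 4 and week 8, in clinic or by telephone. Data processing and storage dates the last two as 28±2 and 56±2 days. Neither says whether these contacts apply after withdrawal. The section headed Patient compliance and withdrawal deals only with reminders and course completion.

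**The concern.** The duty to record AEs attaches to the subject and lasts to the end of the study. The withdrawal rule removes the status of subject at the moment treatment stops, and does so although the participant still consents. The protocol therefore gives a site two instructions about the same person and no way to rank them.

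Two kinds of loss are possible. Events after withdrawal may not be recorded, because the person is no longer a trial subject. Events recorded before withdrawal may not be reported, because the person is out of the analysis. The second possibility also sits badly with the promise to list AEs that arose during the trial.

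With ten hospitals taking part, different sites may settle the question differently, and AE observation would then depend on local reading. A statistical analysis plan cannot repair this afterwards: whom to contact for AEs, and until when, is a matter of conduct, and data not collected cannot be analysed.

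**Working it through.** The protocol states no figure on this point, so there is none to reproduce. The check is a comparison of the rules for one case: a participant who stops treatment at the researcher's request and has not withdrawn consent.

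| Question | Withdrawal rule (Eligibility criteria) | AE Reporting | Statistical methods |
|---|---|---|---|
| Still a trial subject? | No, from that moment | Period is tied to the subject; withdrawn participants not mentioned | Not addressed |
| AEs recorded afterwards? | Not stated | Yes, read alone | Not addressed |
| AEs already recorded are reported? | Out of the analysis | Not addressed | Yes, if the listing counts as separate from the analysis |
| Does standing consent matter? | No, by its own terms | Not addressed | Not addressed |

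1. *After withdrawal.* If the word subject in the AE section has the meaning that the withdrawal rule gives it, the recording duty lapses at withdrawal. If the duty to record to the last study day is read on its own, it continues. Both readings fit the text.
2. *Before withdrawal.* If the AE listing belongs to the study's analysis, the withdrawal rule removes the person's earlier events from it. If the listing stands apart, the events stay. Again both readings fit.
3. *Time at stake per person.* Follow-up ends at 56±2 days, so at most 56 + 2 = 58 days from day 1, or about eight weeks. A participant who stops before the day 28 contact could lose two scheduled contacts. One who stops between the day 28 and day 56 contacts could lose one.
4. *Number of people affected.* This cannot be derived. The protocol gives no expected number of participants who stop treatment with consent intact, for deterioration or any other reason.

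**The case against.** The strongest reply is that the two rules can coexist. The withdrawal rule speaks of subject status and of the analysis. It does not mention AE recording, the case report form or follow-up contact, so a site could leave a person out of the analysis and still document AEs to the end. This stands in part. It rules out saying that such events will certainly be lost, or that no site could comply with both sections. It does not remove the ambiguity, because the AE period is written in terms of the very status that the withdrawal rule takes away.

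Four stronger readings are tempting, and the document does not support them.

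- *Harm is concentrated in the patients removed.* A reader might infer this from the mention of deterioration. The disease is premature ejaculation, so deterioration may simply mean worse symptoms, which PEDT and IELT already measure. The same rule also covers voluntary drop-outs and those judged unsuitable.
- *The loss can be sized from the sample size section.* The 20% maximum loss on 300 patients gives 0.20 × 300 = 60 people. That is an all-cause ceiling on loss to follow-up. It is not a rate of withdrawal with standing consent, and it includes people whom no wording would reach.
- *Only drop-out reasons are kept.* The Statistical methods section does plan an AE listing. The question is whom it covers.
- *A comparison of AEs between arms would be biased.* The trial is open-label and removal is partly at the researcher's discretion, so removal could differ by arm. But the protocol plans a listing, not a between-arm test, and AEs are neither a primary nor a secondary outcome.

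It is also fair to say that the stakes are moderate: the randomised difference is a WeChat course added to conventional treatment, over about eight weeks.

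**Conclusion.** The conflict is real and should be corrected. Taken together, the withdrawal rule, the AE recording rule and the AE listing do not settle whether AEs of a participant who stops treatment but keeps consent are collected to the end of the study, or reported at all. Such events, after withdrawal and possibly before it, may go unrecorded or unreported, and sites may differ.

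The conclusion rests on the wording alone and on no assumed rate. Per person the exposure is bounded at about eight weeks of AE observation. Across the trial the size is unknown. The point concerns safety data only: restoring withdrawn patients to the efficacy analysis would not by itself oblige sites to keep collecting their AEs.

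**What to change.** Reconcile the withdrawal paragraph, Adverse Event Reporting and Statistical methods by adding that:

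1. stopping study treatment without withdrawing consent does not end AE collection, which continues to the last study day;
2. the day 28 and day 56 contacts already scheduled, in clinic or by telephone, are used to collect AEs from these participants;
3. the AE listing covers all randomised patients, including events recorded before withdrawal.

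The withdrawal criteria need no change, and there is no need to require that every deterioration be classed as an AE. The cost is a few sentences of protocol text and some effort to reach patients who have stopped treatment. No new visits are added.

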**Data processing and storage**

Data collection will occur at four time points: baseline, day 1 of intervention period, 28±2 days, and 56±2 days. The collected data will be stored in the form of electronic case report forms (CRFs). Clinical research coordinators (CRC) will complete the electronic CRFs. Researchers will be informed of any changes/edit checks completed by the CRC and the system automatically. Throughout the study process, authorized researchers will be allowed to access the study computer and assess the data.

**Sample size**

This study adopted two control groups, namely, the remote management + conventional treatment group and the conventional treatment group, with a 2:1 ratio for enrollment. The primary research indicator was the PEDT score, with α=0.05 and β=0.2. Previous literature has shown that the PEDT score decreases by at least 2-3 points with psychological/behavioral therapy [20] and by at least 6-7 points with drug therapy [21, 22]. Given a maximum follow-up loss rate of 20% for each group, a target sample size of 300 patients, with 150 patients in each group, was determined.

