**Trial design**

This study is a multicenter, randomized, controlled, open-label parallel-group exploratory trial, consisting of an intervention group and a standard treatment group. Participants will be randomly assigned in a 2:1 ratio to evaluate the efficacy of CBT in improving ejaculatory control in patients with PE. The study will be conducted from May 2023 to Dec 2024 at ten hospitals in China, primarily including the First Affiliated Hospital of Sun Yat-Sen University. The study protocol follows the Standard Protocol Items: Recommendations for Interventional Trials (SPIRIT).

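### The protocol fixes 2:1 allocation but sets the target at 150 patients per group, which is 1:1; the ratio, group sizes and total must be reconciled

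*Protocol*

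**What the plan says.** The Trial design section fixes the allocation: "Participants will be randomly assigned in a 2:1 ratio". The Sample size section names the two arms (remote management plus conventional treatment, and conventional treatment alone) and repeats the ratio: "with a 2:1 ratio for enrollment".

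The same paragraph then gives the basis of the calculation. The error rates are in "The primary research indicator was the PEDT score, with α=0.05 and β=0.2". The effect is described only through changes seen in the literature, such as "the PEDT score decreases by at least 2-3 points with psychological/behavioral therapy", with a larger decrease quoted for drug therapy. Attrition is in "Given a maximum follow-up loss rate of 20% for each group". The paragraph closes with "a target sample size of 300 patients, with 150 patients in each group, was determined".

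The Group therapy section refers to a randomisation table and a randomisation system but gives no ratio.

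**The concern.** Equal groups of 150 are a 1:1 design. A 2:1 design with 300 patients has 200 in one arm and 100 in the other. The conflict lies within a single paragraph of the Sample size section, and again between that paragraph and Trial design.

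Three things depend on which statement is right: the randomisation table, the recruitment target for each arm, and the power attached to the primary PEDT comparison. The smaller arm is either 100 or 150, a gap of 50 patients. At a fixed total and with equal SDs, an unequal split is also less precise than an equal one, so a power statement that holds for 150/150 does not carry over unchanged to 200/100.

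**Working it through.** **Inputs from the protocol.** Ratio 2:1 (Trial design; Sample size). Total 300 and 150 per group (Sample size). α = 0.05, sidedness not stated; β = 0.2. Loss of 20% in each group. Not given: the SD, the between-group difference and the formula. The PEDT decreases quoted are changes under a treatment, not a difference between the arms.

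**Can the figure of 300 be reproduced?** No. Without an SD and a between-group difference, 300 can be neither confirmed nor refuted. The check below therefore compares the two splits of the same 300 patients.

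**Step 1: group sizes.**
- 1:1: 300/2 = 150 per arm; after 20% loss, 150 × 0.8 = 120 per arm.
- 2:1: 300 × 2/3 = 200 and 300 × 1/3 = 100; after 20% loss, 160 and 80.

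**Step 2: precision.** With equal SDs, the variance of the difference in means is SD² × (1/n₁ + 1/n₂).
- 120/120: 1/120 + 1/120 = 0.01667
- 160/80: 1/160 + 1/80 = 0.01875
- Ratio: 0.01875 / 0.01667 = 1.125, so 12.5% more variance, whatever the effect or SD.
- Equivalently, the relative efficiency is 4 × (2/3) × (1/3) = 0.889, so 300 patients at 2:1 carry the information of about 267 at 1:1.

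**Step 3: detectable difference at 80% power.** Normal approximation, two-sided 5% (assumed): d = (1.960 + 0.842) × √(1/n₁ + 1/n₂), in SD units.
- 120/120: 2.802 × 0.1291 = 0.362
- 160/80: 2.802 × 0.1369 = 0.384, which is 6.1% larger.

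**Step 4: power if 150/150 was sized for exactly 80%.** Hold d = 0.362 and change the split: 0.362 / 0.1369 − 1.960 ≈ 0.68, and Φ(0.68) ≈ 0.752. Power falls from 80.0% to 75.2%. With a one-sided 5% test it falls to 75.8%.

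**Step 5: range.** The differences and SDs below are assumptions for illustration; they are not in the protocol.

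| Assumed difference, SD | Power at 120/120 | Power at 160/80 |
|---|---|---|
| 2, 6 | 73.3% | 68.2% |
| 2.5, 7 | 79.0% | 74.2% |
| 3, 8 | 82.8% | 78.2% |
| 2, 5 | 87.3% | 83.2% |
| 3, 5 | 99.6% | 99.2% |

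In these cases the loss runs from about 5 percentage points to under 1. Depending on the inputs, 80% is met by both splits, by 120/120 only, or by neither.

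**Step 6: what each resolution implies for the total.**
- 1:1 keeps 300 as 150/150.
- 2:1 with 300 is 200/100.
- 2:1 with 150 in the smaller arm is 300 + 150 = 450.
- To keep at 2:1 the precision that 150/150 gives, the total is 300 × 1.125 = 337.5. The next multiple of three is 339 (226/113).

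**The case against.** The strongest counter-argument accepts the contradiction but disputes what follows from it. A reader might infer that the trial is underpowered or that it misses its stated beta. The protocol does not support that. It gives no SD, between-group difference or sidedness, so the calculation may have been done for 2:1, for 1:1, or with ample margin. Under some plausible inputs in the table, 160/80 still exceeds 80%. This part of the objection stands: the fall from 80% to 75% is conditional, and only the 12.5% increase in variance at a fixed total is firm, given equal SDs.

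A reader might also infer that, because 2:1 appears twice and 150 per group once, the arms are really 200/100. The repetition favours 2:1 but does not prove it. The ratio, the group sizes or the total could each be the slip.

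It is also tempting to say that centres might close an arm at the wrong count. Nothing in the protocol supports this, since the Group therapy section assigns patients through a randomisation system and not by filling arms to a quota.

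Finally, Trial design calls the study exploratory, which lowers the weight of a modest power loss. It does not excuse the inconsistency: the protocol chose to state a ratio, error rates and group targets, and these should describe one design. The statistical analysis plan is not at hand. It might say which design is meant, but it could not make both protocol statements true.

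**Conclusion.** The point holds as an internal contradiction on a basic design parameter: 2:1 allocation, a total of 300 and 150 per group are incompatible. This needs no assumption and should be corrected. The severity rests on the irreconcilable allocation statements, not on a proven loss of power.

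The statistical consequence is limited. If 2:1 with 300 is what is run, the between-group variance is 12.5% larger than at 150/150 and the detectable difference 6.1% larger, assuming equal SDs and equal 20% loss. Power would be about 75% only if 150/150 was sized for exactly 80% with a two-sided 5% test. With a larger margin the reduction shrinks, and the stated beta may still be met.

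**What to change.** Make the ratio, the group sizes, the total and the randomisation table agree, by one of these routes:

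- **If 1:1 was intended:** change the ratio to 1:1 in both Trial design and Sample size and keep 150/150. The total does not change.
- **If 2:1 was intended with 300 patients:** replace the group sizes by 200 and 100 (160 and 80 evaluable after 20% loss), say which arm is the larger, and restate the power or detectable difference for that split from the sponsor's own SD and between-group PEDT difference. For reference, 300 patients at 2:1 detect about 0.38 SD with 80% power, against 0.36 SD at 150/150. These figures are back-calculated from the total. If shown, they should be labelled as what 300 patients deliver, not as a design assumption.
- **If 150 was meant for the smaller arm:** the total is 450, not 300, and must be stated and justified as such.

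If randomisation has begun, the table in use shows which ratio was implemented, and the text should say so openly.

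The first route costs a short text correction. The second costs the same plus a slightly less favourable detectable difference. If the sponsor's inputs then show less than 80% power, the choice is to accept the lower power or raise the total; 339 randomised would restore the precision of 150/150. The third route would add 150 patients.
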